**Fig. 2 fig2:**
[figure not shown]
Administration schedule.

### Data collection

2.9

All the patients provide written informed consent to participate in the study and are asked to complete a medical history. Clinical data obtained in the ESCAPE study include the ECOG performance status, physical examination findings (e.g., height, body weight, body temperature, and blood pressure), results of hematologic examination (e.g., red blood cell count, hemoglobin, hematocrit, platelet count, white blood cell count, and differential count of leucocytes), results of blood biochemical examination (e.g., liver enzymes, alkaline phosphatase, total bilirubin, total protein, albumin, creatinine, lipids, fasting blood sugar, hemoglobin A1c, C-reactive protein, and electrolytes), results of urinalysis, chest X-ray imaging, lung to pelvic CT or MRI, brain CT or MRI, bone scintigraphy, electrocardiography, and the questionnaires for HRQOL (e.g., EORTC QLQ-C30, FKSI-DRS, EQ-5D). The X-ray, brain CT, and bone scintigraphy are performed at the time of study registration. Other examinations are performed every 2 months from the date of the commencement of treatment to month 24 and every 3 months after month 24 until the study is completed (Fig. 3). However, examinations can be performed at any time, if the clinical investigator considers them to be necessary.

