### Administration of IFNα plus IL-2 vs. first-line therapy with sunitinib followed by second-line with axitinib

2.8

Patients assigned to cytokine group receive intravenous injection of IL-2 at a dose of 700,000 unit/day five days/week for the initial 2 or 4 weeks, and then, one or three times/week as maintenance plus subcutaneous injection of IFNα 5–6 million units two or three times/week (Fig. 2). Sunitinib at a dose of 50 mg/day is orally administered to patients who are assigned to the sunitinib group, and one course consists of 4 weeks of administration and 2 weeks of withdrawal. A schedule of 2 weeks of administration and one week of withdrawal is also permitted. Reduction of doses is permitted if a clinical investigator considers the basic doses inappropriate for any reason. The administration of IL-2 plus IFNα or sunitinib is terminated when progressive disease (PD) is confirmed based on RECIST v.1.1, the patient dies, or severe AEs occur. A clinical investigator administers axitinib as second-line treatment immediately after confirmed comprehensive evaluation of PD based on RECIST v.1.1 during first-line treatment. In case of cessation of first-line treatment because of severe AEs, a clinical investigator may consider restarting first-line treatment after recovery below grade 2. Axitinib at a dose of 10 mg/day (5 mg dose twice per day) is orally administered to patients as second-line treatment. Dose reduction or dose increase up to 20 mg/day (10 mg dose twice per day) is permitted if a clinical investigator considers the basic doses inappropriate for any reason. The administration of axitinib is terminated when PD is confirmed by comprehensive evaluation based on RECIST v.1.1, the patient dies, or severe AEs corresponding to discontinuation criteria occur. Zoledronic acid and denosumab are permitted for patients with bone metastasis.

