### Definition of endpoints

2.10

The primary endpoint is total progression-free survival (PFS) from randomization to PD based on RECIST v.1.1 criteria examined with CT or MRI or death during second-line therapy. PD during first-line therapy is not counted as an event based on the definition. In case of cancellation during first-line therapy caused by severe AEs or refusal of patient without confirming PD, the end date of first-line therapy is not counted as cessation, and the case continues to receive the second-line therapy.

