### Seven secondary endpoints are set in the ESCAPE study

2.11

1.OS, defined as the time from randomization to death from any cause.2.Each PFS in first-line treatment and second-line treatment based on RECIST v.1.1 criteria.3.Objective response rate (ORR), defined as the proportion of CR and partial response (PR) cases in total cases based on best overall response using RECIST v.1.1 criteria, and disease control rate (DCR), defined as the proportion of CR, PR, and stable disease (SD) cases in total cases in first-line and second-line treatment.4.Time to treatment failure (TTF), defined as the time from commencement of first-line therapy to earliest time of PD using RECIST v.1.1 criteria, death from any cause, or cancellation of therapy in first-line treatment.5.Total TTF from first-line to second-line treatment, defined as the time from commencement of first-line therapy to earliest time of PD using RECIST v.1.1 criteria, death from any cause, or cancellation of the therapy in second-line treatment.6.Safety in first-line and second-line treatment evaluated by Common Terminology Criteria for Adverse Events v4.0 system.7.HRQOL in first-line and second-line treatment evaluated by EORTC QTQ-C30, FKSI-DRS, and EQ-5D.

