### Sample size consideration and anticipated completion of enrollment

2.13

Based on the AXIS trial (second-line axitinib versus sorafenib) reported by Rini et al. [2] and the reports from Akaza et al. [11], the median total TTF would be calculated as 26.1 (10.4 + 15.7) months for combination of INFα + IL-2 and axitinib, and 15.3 months (10.5 + 4.8) for the combination of sunitinib and axitinib. In this study, hypothetical median TTFs were set for 26 months in the combination of INFα + IL-2 and axitinib and 15 months for the combination of sunitinib and axitinib. We calculated the sample size from the study duration of 5 years (two-year entry period and three-year observation period) and the difference in total TTF between the groups. To detect a significant difference between the groups by a log-rank test with significant level of 0.05 and power of 80%, at least 65 patients in each group are required. Furthermore, given the assumption that approximately 10% of randomized patients will not be evaluated for various reasons, the target sample size was set at 72 patients per group (total 144 cases).

The final patients were enrolled in September 2017, and the entire study will be completed by September 2020.

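### CT/MRI is scheduled from the start of treatment but total PFS is timed from randomisation, so a start delay that differed between the arms would bias the primary comparison slightly

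*Protocol article*

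**What the plan says.** Three places in the protocol article bear on this.

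- **Scan calendar (2.9 Data collection).** Examinations beyond those done at registration take place "every 2 months from the date of the commencement of treatment to month 24 and every 3 months after month 24 until the study is" over. Chest X-ray, brain imaging and bone scintigraphy belong to registration, so the repeated examinations include the lung-to-pelvis CT or MRI. The same section adds that "examinations can be performed at any time, if the clinical investigator considers them to be necessary".
- **Primary endpoint (2.10 Definition of endpoints).** "The primary endpoint is total progression-free survival (PFS) from randomization to PD based on RECIST v.1.1 criteria examined with CT or MRI". A patient's death while on second-line treatment also counts. The clock starts at randomisation.
- **Secondary endpoints (2.11).** "Time to treatment failure (TTF), defined as the time from commencement of first-line therapy to earliest time of PD". TTF and total TTF start with treatment, so they share the scan calendar's origin. Total PFS does not.

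The calendar rule is worded identically for both arms. The article gives no interval from randomisation to first dose, overall or by arm.

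**The concern.** Progression is seen only at scans two or three months apart, so recorded events cluster at visits. If one arm's calendar runs a little late on the randomisation clock, then at every cycle the other arm's progressions are counted while all the late arm's patients still appear progression-free. The log-rank test and the Cox model (2.14) both work on the order of events, so they read this as a benefit for the later-starting arm.

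A difference in start is conceivable here. Assignment is known before treatment begins. One arm takes oral sunitinib. The other receives "intravenous injection of IL-2 at a dose of 700,000 unit/day five days/week for the initial 2 or 4 weeks" plus subcutaneous IFNα (2.8), which may take longer to arrange. If so, the error would favour the experimental arm in the primary analysis.

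**Working it through.** **Inputs from the article.** Scan grid at months 2, 4, …, 24, 27, 30, … (2.9). Recruitment from October 2013 to September 2017, 48 months (2.7). Completion by September 2020 (2.13), hence about 36 months of follow-up for the last patient and 36 + 48 = 84 for the first. Target 72 per arm, with "hypothetical median TTFs were set for 26 months in the combination of INFα + IL-2 and axitinib and 15 months" for sunitinib then axitinib (2.13). Two-sided 5% log-rank test and Cox model (2.14).

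**Assumed.** The start delay, with the cytokine arm later by 0, 0.25, 0.5 or 1 month.

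**The plan's own figure.** The design hazard ratio is 15/26 = 0.577. Schoenfeld events: 4 × (1.96 + 0.84)² / (ln 0.577)² ≈ 104. With 24 months' entry and 36 months' further observation, the exponential event probabilities are 0.886 and 0.717, mean 0.801. Then 104 / 0.801 / 2 = 64.9, so the stated 65 per arm reproduces. The scan origin does not enter this calculation.

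**Rough size of the bias.** Let p be the probability of progressing between two scans, with n at risk in each arm and the late arm scanned just after the other.

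- At the early arm's scan, np events occur and np/2 are expected in that arm.
- At the late arm's scan, np events occur, and the early arm's expected share is np(1−p)/(2−p).
- The early arm's net excess is np/2 − np(1−p)/(2−p) = np·p/[2(2−p)].
- Dividing by the log-rank variance, about 2np/4 = np/2, gives a false log hazard ratio of about p/(2−p).

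For a 15-month median and a 2-month interval, p = 1 − 2^(−2/15) = 0.088, so p/(2−p) = 0.046 and the hazard ratio is exp(−0.046) = 0.955. This advantage hardly depends on the length of the delay. It is partly offset because the late arm's first interval is longer and collects more events at its first scan. That offset grows with the delay, so a longer delay need not mean more bias.

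**Simulation.** 6,000 trials per scenario, 72 per arm, exponential progression times, progression dated at the first scan after it occurs, and the follow-up above. The hazard ratio is cytokine/sunitinib. In the null scenarios both medians are 15 months.

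| Assumed extra delay (months) | Null HR, exact visits | Two-sided rejection | Rejection favouring late arm | Null HR, ±1 week visits and 0–2 week start spread | Two-sided rejection |
|---|---|---|---|---|---|
| 0 | 1.002 | 5.5% | 2.6% | 1.003 | 5.5% |
| 0.25 | 0.955 | 6.7% | 5.0% | 0.979 | 6.0% |
| 0.5 | 0.966 | 6.3% | 4.4% | 0.971 | 6.2% |
| 1 | 0.989 | 5.7% | 3.2% | 0.989 | 5.8% |

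The Monte Carlo standard error of a 5.5% rejection rate is √(0.055 × 0.945 / 6000) = 0.3 percentage points.

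With true medians of 26 and 15 months and exact visits, the estimated hazard ratio is 0.590 with no delay and 0.560, 0.565 and 0.577 at the three delays. Power is 84.6%, 89.6%, 88.8% and 86.4%.

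**Scans counted from randomisation, cytokine start 0.25 month later.** The null hazard ratio is 1.002 with 5.5% rejection. Under 26 versus 15 months it is 0.590 with 84.6% power. These are the no-delay values.

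**The case against.** The strongest objection is that the premise is undocumented. The rule is the same for both arms, an equal delay produces no bias, and a schedule of frequent injections describes dosing, not a late start. This stands: the bias is conditional, and its direction is not established.

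Other objections limit the size.

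- **Visit and start scatter.** Real visits vary, and the middle columns show the effect shrinking at the shorter delays when they do. Unscheduled examinations loosen the grid further.
- **Deaths.** They count as events and need no scan. The simulation has none.
- **The endpoint has two stages.** Progression on first-line therapy is not an event. A two-stage model (medians 10.5 and 4.8 months) gives 0.95 to 0.96 with exact visits and 0.97 to 0.99 with scatter if the calendar runs on through axitinib. If the calendar restarts at axitinib, it gives 0.98, and 0.98 to 1.00 with scatter. Section 2.9 mentions no restart.

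A reader might infer three stronger things that the article does not support.

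- **A false hazard ratio of 0.93 to 0.94.** This results from exact visits with everyone censored at month 36. Month 36 is itself a scan date, so the punctual arm's scan counts and the delayed arm's is cut off. Actual follow-up runs from about 36 to 84 months.
- **That the comparison is biased towards cytokines.** No arm-specific start interval is reported.
- **That patients who never start treatment go unscanned.** An article may leave their handling to the full protocol, so its absence here is no finding.

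**Conclusion.** The mismatch is real and is a stated rule, not an omitted detail: scans run from first dose and the primary endpoint from randomisation. Its consequence depends on a difference in start delay that the article does not report. For an assumed difference of 0.25 to 1 month, the hazard ratio under equal true PFS is about 0.95 to 0.99. Two-sided rejection rises from 5.5% to at most about 6.7%, and rejections favouring the later-starting arm rise from 2.6% to at most 5.0%. On the log scale the largest shift is 0.046 against a planned 0.550, about one twelfth. With no difference the bias is nil. These figures rest on exponential times, a single calendar and no deaths. The point is minor, but the error would be systematic and is cheap to remove.

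**What to change.** In 2.9, schedule CT/MRI every 2 months, and every 3 months after month 24, from the date of randomisation in both arms, whatever the start date or dose delays. Leave laboratory and other safety visits timed from first dose.

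This is one sentence, with no extra scans and no change to the sample size. The costs are that imaging and laboratory visits may not coincide, and that a late starter's first scan comes slightly sooner after first dose. Enrolment closed in September 2017, so only the remaining scans can be re-anchored. For those already done, tabulating the interval from randomisation to first dose by arm would show whether the bias could have arisen.

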**Fig. 3 fig3:**
[figure not shown]
Follow-up schedule.

### Definition of endpoints

2.10

The primary endpoint is total progression-free survival (PFS) from randomization to PD based on RECIST v.1.1 criteria examined with CT or MRI or death during second-line therapy. PD during first-line therapy is not counted as an event based on the definition. In case of cancellation during first-line therapy caused by severe AEs or refusal of patient without confirming PD, the end date of first-line therapy is not counted as cessation, and the case continues to receive the second-line therapy.

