## Introduction

1

Recently developed molecular target drugs and immune checkpoint inhibitors have changed treatment strategies for metastatic renal cell carcinoma (mRCC) because of their efficacy; however, complete recovery from mRCC remains very rare [[1], [2], [3]]. Therefore, our current realistic goal for mRCC treatment would be maximum elongation of overall survival (OS) of patients while maintaining their quality of life (QOL). To achieve the goal, we must plan longitudinal treatment strategies that consider the general condition of the patient and control adverse events (AEs) of administered drugs. However, an appropriate protocol for sequential treatment of mRCC has yet to be established. The number of patients who can undergo treatment is gradually decreasing, as the treatment lines are increasing to second-, third-, and fourth-line, because the general condition of patients worsens with disease progression and/or AEs of the drugs. To extend OS of patients with mRCC as long as possible, selecting the first-line and consecutive second-line therapy is extremely important. Based on the guidelines for mRCC treatment and the current Japanese system of national insurance, the recommended drug selection for mRCC categorized as favorable risk by the Memorial Sloan-Kettering Cancer Center (MSKCC) criteria [4,5] is sunitinib [1] or pazopanib [3] as first-line drug, and axitinib [2] or nivolumab [6] as second-line. However, OS in patients treated with cytokines, which have been used for a long time for mRCC in Japan, has been reported to be better than in western countries [7]. Therefore, it is speculated that the effectiveness of cytokines is better for Japanese patients than for western patients. Some mRCC cases meeting favorable risk criteria were reported to have achieved complete remission (CR) and durable response using interferon alfa (IFNα) + low dose interleukin-2 (IL-2) [8,9]; however, molecular targeted treatments may not achieve CR for patients with mRCC. Cytokine therapies are not effective in patients with high risk mRCC, but cytokine therapy may be effective for some patients with intermediate risk mRCC, because patients with intermediate risk mRCC are part of a heterogenous group [10].

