### Planned statistical analyses

2.14

Intention-to-treat analyses in each group will be performed, and survival curves will be estimated with Kaplan-Meier method. A log-rank test will be used to evaluate differences in the survival curves between the two groups of patients. Hazard ratio will be estimated with the Cox proportional hazard model. Restricted mean survival time will be considered to quantify the treatment benefit in the absence of proportional hazard assumption in survival curves. ORR (CR + PR) and DCR (CR + PR + SD) in each group using the best response evaluated by RECIST v1.1 will be estimated for 95% confidence interval with Clopper-Pearson method. AEs in each group will be aggregated by grades and types, and the proportion of AEs will be compared between the groups by Fisher's exact test. The chronological changes in the HRQOL from the baseline evaluation using EORTC QLQ-C30, FKSI-DRS, and EQ-5D will be compared. All the tests will be two-sided, and a *P*-value of 0.05 will be considered statistically significant.

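### As worded, total PFS gives no event to deaths outside second-line therapy or to progression in patients who never start axitinib

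*Protocol article*

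**What the plan says.** Section 2.10 of the Protocol article measures total PFS from randomisation to "PD based on RECIST v.1.1 criteria examined with CT or MRI or death during second-line therapy". It then adds: "PD during first-line therapy is not counted as an event based on the definition". For patients who leave first-line therapy without progression, because of severe adverse events or refusal, it says that "the end date of first-line therapy is not counted as cessation, and the case continues to receive the second-line therapy". It gives no rule for those who do not go on.

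Other sections bear on this:

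- Section 2.8 says that first-line treatment "is terminated when progressive disease (PD) is confirmed based on RECIST v.1.1, the patient dies, or severe AEs occur", so death on first-line therapy is foreseen.
- The Introduction says of mRCC treatment in general: "The number of patients who can undergo treatment is gradually decreasing, as the treatment lines are increasing". The reason given is "because the general condition of patients worsens with disease progression and/or AEs of the drugs". No rate is stated.
- Section 2.14: "Intention-to-treat analyses in each group will be performed". Patients who never reach axitinib therefore stay in the primary comparison.
- Section 2.11 counts death from any cause, without tying it to second-line therapy, for OS (item 1) and first-line TTF (item 4). Total TTF (item 5) also names death from any cause, but the sentence ends by referring to second-line treatment.

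**The concern.** A progression-free survival endpoint should count every death. This one ties death to a treatment line that not every randomised patient will reach. The patients left without an event include some of the worst outcomes: those who die early and those who progress and become too ill for the next drug. If they are censored, the censoring depends on prognosis, and the Kaplan-Meier, log-rank and Cox methods of section 2.14 assume that it does not.

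At stake is the primary result. An arm that loses more patients before axitinib would look better for losing them. First-line treatment is what differs between the arms, so unequal loss is possible.

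**Working it through.** **1. Patient paths against the wording of section 2.10**

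| Path | Event as worded? |
|---|---|
| Progression or death on axitinib | Yes |
| Progression on first-line, then axitinib | Not at first-line progression; a later event counts |
| Death on first-line therapy | No: not during second-line |
| First-line progression, axitinib never started | No: first-line progression is excluded and there is no second line |
| First-line stopped without progression, axitinib never started, later progression or death | No: the text assumes second-line follows |
| Axitinib stopped without progression, then death | No: not during second-line |
| Still on first-line without progression at data cut-off | Censored, correctly |

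However the sentence is parsed, the reference to second-line therapy qualifies death.

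**2. The plan's own sample size (section 2.13)**

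- Hazard ratio = 15/26 = 0.577.
- Schoenfeld events, two-sided 0.05, 80% power: 4 × (1.960 + 0.842)² / (ln 0.577)² ≈ 104.
- Event probability with uniform entry over A = 24 months and F = 36 months' further observation: 1 − [exp(−λF) − exp(−λ(A+F))]/(λA), with λ = ln 2/median. This gives 0.717 (26 months) and 0.886 (15 months), mean 0.801.
- Patients per arm = 104/0.801/2 = 64.9, so 65. Adding 10%: 65 × 1.1 = 71.5, so 72.

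The stated figures reproduce. The calculation uses total medians only and has no term for patients who never reach axitinib, so the repair leaves it unchanged.

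**3. Direction within an arm**

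Turning an event into a censored time removes a downward step from the Kaplan-Meier curve and adds none. The as-written curve therefore lies on or above the curve that counts these failures.

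**4. Size between arms (simulation)**

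Model: first-line and second-line durations are exponential. A share q of patients, assumed for each arm, never reaches axitinib. *Counted* makes these patients events at the end of first-line; *as written* censors them there. There are 72 patients per arm, 48 months' entry (section 2.7) and 36 months' further follow-up (section 2.13). Medians in months are 10.4 then 12 for cytokine and 10.5 then 4.8 for sunitinib (section 2.13; the 12 is from the Discussion). Hazard ratios are cytokine over sunitinib; rejection is by two-sided log-rank test at 0.05. Repeated runs agree to about 0.01 in the hazard ratio.

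| Assumed loss, cytokine / sunitinib | HR counted | HR as written | Rejection, counted → as written |
|---|---|---|---|
| 5% / 5% | 0.59 | 0.58 | 83% → 82% |
| 20% / 20% | 0.64 | 0.59 | about 70% either way |
| 15% / 10% | 0.63 | 0.57 | 70% → 81% |
| 35% / 20% | 0.74 | 0.55 | 40% → 82% |
| 20% / 35% | 0.60 | 0.69 | 78% → 39% |

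A 10% / 15% loss gives 0.594 against 0.605. At an equal 20% loss both medians rise by about 4 to 6 months.

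Section 2.13 uses 15.7 months, not 12, for axitinib after cytokine. With 15.7, rejection in the 35% / 20% case is 68% counted and 97% as written.

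**5. Events under the planned design**

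With 65 per arm, 24 + 36 months, the section 2.13 component medians and an equal 20% loss, events fall from 110 to 85, against the 104 required. Power still does not fall in that scenario (88% counted, 90% as written).

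**6. Identical line durations in both arms**

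With an equal 20% loss, rejection is 5.4% counted and 5.6% as written. With 10.5 then 4.8 months in both arms and 30% against 10% lost, the hazard ratio is 1.08 counted and 0.84 as written, in favour of the arm that loses more; rejection as written is about 15%.

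The simulation does not cover deaths after axitinib stops without progression.

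**The case against.** The strongest reply is that the article states no censoring rule. The only event it excludes in so many words is first-line progression; the exclusion of first-line death follows from where a phrase sits. The endpoint is still called progression-free survival, and a full protocol or SAP, not shown here, could deal with patients who never start the next line. It is right that censoring is an inference. But the event definition itself is stated, and on its plain reading it omits these deaths. A later rule that counted them would depart from the published definition, so this is more than detail left to another document.

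Second, the evidence for loss is thin. The Introduction's remark is general background. Entry is limited to favourable or intermediate risk, ECOG 0–1 and a life expectancy above 3 months. Section 2.8 has axitinib follow promptly on confirmed progression. Loss may therefore be small, and at an equal 5% the hazard ratio hardly moves. This stands, and it limits the claim about size.

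Third, a reader might infer that the trial has an inflated type I error, or that the definition favours one particular arm. The documents support neither. Type I error stays near 5% when loss is equal. The 15% in step 6 is not a clean null, because arms that lose 30% and 10% do differ once loss counts as failure. With 10.4 and 12 months in both arms, the counted rule rejects more often (14.6%) than the written one (8.9%). The Discussion calls sunitinib's adverse events more severe in Japanese patients, but section 2.10 sends patients who stop for adverse events on to second-line therapy, so that remark does not settle which arm loses more.

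**Conclusion.** The definition is wrong as written. Section 2.10 gives no event to deaths outside second-line therapy or to progression in patients who never start axitinib. Yet section 2.8 foresees death on first-line therapy, and section 2.14 keeps all these patients in an intention-to-treat comparison.

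Upward bias of each arm's curve follows whenever such patients exist and are censored. Bias in the hazard ratio is conditional: negligible at a small equal loss, modest at an equal 20%, and material mainly when the loss differs by arm. Even 15% against 10% moves it from 0.63 to 0.57. These sizes rest on assumed loss shares, exponential durations and the component medians chosen. The documents reveal neither the size nor the direction of the bias in this trial. The point deserves correction because the primary result would otherwise depend on an unknown quantity that arises after randomisation.

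**What to change.** Before database lock, amend section 2.10 as follows:

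- Total PFS runs from randomisation to the earlier of RECIST v.1.1 progression after the start of second-line therapy and death from any cause at any time (before, during or after second-line therapy).
- For patients who never start second-line therapy, RECIST progression is the event, whether on first-line therapy or after it, including after stopping without progression.
- *Never started* is defined by a prespecified time window, because classing a first-line progression as an event otherwise depends on open-ended later information.
- Stopping axitinib without progression does not censor.
- A sensitivity analysis counts only death as the event for patients who never start second-line therapy.

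For total TTF (section 2.11, item 5), keep cancellation as an event; copying the PFS wording would remove it. State that death from any cause at any time counts and that ending first-line therapy without starting second-line is a failure.

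The cost is an endpoint amendment and somewhat shorter medians. No new data are needed: deaths are required for OS and first-line progression for first-line PFS. Only the counting of events changes, not the treatment of patients.
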